### Qualitative data

Following recruitment, we will conduct semi-structured qualitative interviews with a purposive sample of up to eight health professionals in each region (up to 24, based on thematic data saturation) and at least six patients per region (up to 48, based on thematic data saturation). The aim of the interviews is to explore strategies that promote the intervention’s sustained use and rapid implementation, using NPT [50] which has been successfully used before [51, 52].

### Health economic assessment

A cost-effectiveness analysis will be conducted to assess the medico-economic impact of implementing the intervention among patients with lower HL in disadvantaged areas of the four targeted regions. The purpose of this analysis is to compare the costs related to the effectiveness of the intervention with health professionals (the 2-h HL training) and users (brochure and video) versus usual care (control arm). First, we will calculate the cost per additional CRC screening performed by dividing the difference between the costs of implementing the intervention and the cost of the usual care group, relative to the observed increase in testing in the intervention group. Second, we will calculate the cost per new cancer diagnosed in patients with a positive screening test. The time horizon of the analysis will be the duration of the study (1 year).

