### Intervention

We will translate and adapt (using a translation procedure adapted from TRAPD) an intervention previously developed and evaluated in a randomized controlled trial conducted in the US to address HL and improve CRC screening [33]. This intervention combined a 2-h HL and CRC screening training targeting GPs and a patient level intervention consisting of a short brochure and video. To maximize generalizability and implementation, we will develop a 2 h e-learning HL training in French and a one-hour booster session similar to the previous trial’s intervention [33]. The first hour will be an online course that will primarily include didactic teaching using videos. The second hour will consist of a c-MOOC (Connectivist – Massive Online Learning Course), an online classroom model, where all participating GPs in the intervention group can interact with each other and with a trained facilitator from our team, experienced in HL training ([name]). This interactive session will build on the content provided in the initial didactic session. The c-MOOC is based on a learner-driven dialogue where participation, discussions and reflection on the content presented are the intended focus. It will also include small group discussions and role-playing sessions focused on empowering GPs to discuss CRC screening effectively with their patients. A 1-h c-MOOC booster training session will be held 6 months later. During this session, GPs will receive data on their screening uptake rates over the previous 6 months, a reminder of practical strategies to communicate with patients with lower HL skills in busy, high-volume primary care practices. They will also have the opportunity to engage in small group discussions. Each GP in the intervention arm will receive 150 euros for completing the first 2-h learning training (1 h didactic learning + 1 h c-MOOC) and 75 euros for completing the booster session (1 h c-MOOC).

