### Outcome measures

#### Primary outcome measure

The primary outcome measure is CRC screening uptake assessed 1 year after the initial recruitment consultation (T2) by self-report questionnaire (see Table 1). Each CRCDC, in collaboration with the health insurance body (CPAM) in each region, will also provide data on CRC screening uptake at 6 months (for feedback to GPs in the intervention arm) and 1-year post enrollment.

**Table 1 Tab1:** Outcome measures and data collection timepoints for patients

Outcome measures	Timepoints	
	(T1) One week after the primary care consultation where CRC screening is discussed	(T2) 1 year after the CRC screening consultation
Number of eligible patients identified and successfully enrolled	**X**	
Number of patients enrolled who receive the patient-facing intervention	**X**	
Discontinuation rate		**X**
CRC screening uptake (primary outcome) with self-report item		**X**
Screening intention (1 items)	**X**	
Knowledge of CRC screening (2 items)	**X**	**X**
Patient activation (13 items)	**X**	**X**
Health literacy (7 items)	**X**	
EPICES (11 items)	**X**	
SURE (4 items)	**X**	
Was the questionnaire completed alone? (1 item)	**X**	**X**
Demographics (9 items)	**X**	
**Total number of self-report items per timepoint**	**48**	**17**

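### The cost-effectiveness section names only the 2-h GP training, although the intervention also has a separately paid 1-h booster with uptake feedback

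*Protocol article*

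**What the plan says.** The Health economic assessment section of the protocol article sets out the comparison as "the intervention with health professionals (the 2-h HL training) and users (brochure and video) versus usual care (control arm". It then defines a cost per additional screening: the difference in cost between the intervention and usual care, taken "relative to the observed increase in testing in the intervention group". The time horizon is the one-year study. Implementation costs are mentioned but not listed.

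The Intervention section describes a larger GP component: "we will develop a 2 h e-learning HL training in French and a one-hour booster session". On timing it says "A 1-h c-MOOC booster training session will be held 6 months later", and on content that "GPs will receive data on their screening uptake rates over the previous 6 months". The two parts are paid separately: "Each GP in the intervention arm will receive 150 euros for completing the first 2-h learning training", and "75 euros for completing the booster session (1 h c-MOOC".

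The Primary outcome measure section says where the feedback comes from. The regional screening centres, with the health insurance body, will "provide data on CRC screening uptake at 6 months (for feedback to GPs in the intervention arm".

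**The concern.** A cost-effectiveness ratio is interpretable only if its two parts describe the same intervention. Here the effect is 1-year uptake under everything that intervention GPs receive, including the booster and the feedback. The only description of the GP component in the economic section stops at the first two hours.

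If an analyst takes that description as the costing scope, a delivered and paid component drops out of the numerator while its effect stays in the denominator. The error runs one way: it makes the intervention look cheaper per additional screening than it was. The Discussion section presents the training as suitable for national dissemination, so the costed package should match the tested one.

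**Working it through.** The plan states no cost-effectiveness figure, so there is nothing to reproduce. The check compares the sections and then does arithmetic on the stated payments.

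**1. The two descriptions side by side**

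| Component | Intervention section | Health economic assessment |
|---|---|---|
| 2-h GP training | yes, 150 euros per GP | named |
| 1-h GP booster | yes, 75 euros per GP | not named |
| 6-month uptake feedback | yes, data from screening centres and insurer | not named |
| Brochure and video | yes | named |

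**2. Does the booster fall before the outcome?** Under GP recruitment, allocation precedes training and takes place 2 months before patient recruitment opens. Assume that training falls within those 2 months. The booster then comes between month 6 − 2 = 4 and month 6 − 0 = 6 of recruitment, which runs for 12 months (Sample size and power calculation). Patients enrolled in the last 6 to 8 months are seen after it. With even recruitment that is 6/12 to 8/12, or one half to two thirds of patients. The first patient's 1-year outcome falls at month 12, also after it. The booster's effect therefore enters the measured uptake.

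**3. Payments and hours left out.** Inputs: at least 32 GPs planned, so 16 per arm if allocation is equal; all 16 complete both parts (assumed).

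- Training alone: 16 × 150 = 2,400 euros
- Booster: 16 × 75 = 1,200 euros
- Both: 2,400 + 1,200 = 3,600 euros
- Share of payments omitted: 1,200 / 3,600 = 33.3%
- GP hours: 16 × 2 = 32 against 16 × 3 = 48, so 16 / 48 = 33.3% omitted

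**4. Payments per additional screening (illustration).** About 32 patients per GP gives 16 × 32 = 512 per arm. With the planned 15% difference read as percentage points, additional screenings = 512 × 0.15 = 76.8.

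- Training only: 2,400 / 76.8 = 31.25 euros
- With booster: 3,600 / 76.8 = 46.88 euros
- Gap: 1,200 / 76.8 = 15.63 euros

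At the other end, take a 5-point effect (assumed) and 512 × 0.75 = 384 patients after the planned 25% attrition. Then 384 × 0.05 = 19.2 and 1,200 / 19.2 = 62.50 euros. The payment gap is thus about 15.6 to 62.5 euros per additional screening.

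**5. Share of the full ratio.** Let C be all other incremental costs and F the unpriced costs of the booster and feedback (facilitator time, data extraction). The relative understatement is (1,200 + F) / (3,600 + F + C). The documents give neither F nor C, so this share cannot be calculated.

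**The case against.** The strongest reply is that the parenthesis is a descriptive label, not a costing rule. It stands in the sentence on the purpose of the analysis. The sentence that defines the ratio refers to the costs of implementing the intervention, and the Intervention section defines that intervention with the booster. This stands in part: the booster is not expressly excluded, and a careful analyst could include it.

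A second reply is that the 2-h wording is shorthand. The Intervention section sums up the earlier US intervention as a 2-h training and then calls the new 2-h training plus booster similar to it. The Abstract and hypotheses also leave the booster unmentioned. The first observation makes shorthand possible. But for this trial the same section separates the first 2-h part from the booster and pays each on its own. The Abstract and hypotheses speak of training without giving a number of hours, whereas the economic section gives one, and it matches the first part only.

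A third reply is that a condensed article need not list cost items. That is correct, and no cost inventory is asked for here. The point is that the scope the article does state differs from the intervention it describes.

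Two stronger readings are not supported:

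- **The ratio is understated by up to one third.** One third applies to GP payments and GP hours. The documents price neither the other components nor the rest of the booster's cost, and they do not say whether the completion payments count as implementation costs.
- **The denominator is a within-arm change.** The phrase "relative to the observed increase in testing in the intervention group" might suggest this. But the ratio is per additional screening, the comparison is with usual care, and Table 1 schedules the uptake outcome at T2 only. A between-arm difference is already implied.

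**Conclusion.** The inconsistency is real but limited. The stated economic scope leaves out a delivered, separately paid booster and its 6-month feedback, while their effect is counted in 1-year uptake. Applied literally, this understates the cost per additional screening and so favours the intervention.

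The size that can be documented is 1,200 of 3,600 euros in GP payments, together with one third of GP training hours. It rests on 16 intervention GPs who all complete both parts, and on the payments being treated as implementation costs. The effect on the full ratio cannot be determined. The primary outcome, its analysis and the sample size are not affected.

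**What to change.** In the Health economic assessment section, extend the parenthesis on health professionals to read: *the 2-h HL training, the 1-h booster and the 6-month uptake feedback*. The costed intervention then matches the one delivered.

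The change is one phrase and alters nothing in the conduct of the trial. If it is made early, the resources used for the booster and the feedback can be recorded as they arise. The downside is a slightly less favourable ratio.

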**Methods:**

We will use a two-arm multicentric randomized controlled cluster trial with 32 GPs primarily serving underserved populations across four regions in France with 1024 patients recruited. GPs practicing in underserved areas (identified using the European Deprivation Index) will be block-randomized to: 1) a combined intervention (HL and CRC training + brochure and video for eligible patients), or 2) usual care. Patients will be included if they are between 50 and 74 years old, eligible for CRC screening, and present to recruited GPs. The primary outcome is CRC screening uptake after 1 year. Secondary outcomes include increasing knowledge and patient activation. After trial recruitment, we will conduct semi-structured interviews with up to 24 GPs (up to 8 in each region) and up to 48 patients (6 to 12 per region) based on data saturation. We will explore strategies that promote the intervention’s sustained use and rapid implementation using Normalization Process Theory. We will follow a community-based participatory research approach throughout the trial. For the analyses, we will adopt a regression framework for all quantitative data. We will also use exploratory mediation analyses. We will analyze all qualitative data using a framework analysis guided by Normalization Process Theory.

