### Sample size and power calculation

We plan to recruit at least 32 GPs across 4 regions. Based on Ferreira et al.’s trial findings, to detect a 15% difference between the control and intervention arm in CRC screening uptake, with an intra-cluster correlation (ICC) of 0.004 and a 25% attrition rate, a sample size of 1000 people eligible for screening is required [33]. This 15% difference is conservative. The ICC is based on previous studies similar to this trial. Each clinician will be expected to recruit approximately 32 patients, or as many eligible patients as possible if they cannot recruit 32, over the course of 1 year. On average, French GPs have about 300 eligible patients for CRC screening each year. Targeting 32 patients of about 300 represents just under 10%, which is achievable.

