### Randomization

#### Sequence generation, type of randomization and allocation concealment

We will use an R script written by the trial statistician to perform the GP randomization. The random allocation sequence will be concealed until interventions are assigned. We will use block randomization to ensure a balanced allocation of each cluster (GP or GP office) in each region to the intervention and control arms. Participants recruited by GPs will therefore be a priori allocated to either the control or intervention arm by virtue of the GP that has recruited them. GPs will not be required to assess HL or deprivation levels (as these are not a inclusion or exclusion criteria) as the GP practice itself has already been identified as being located in a disadvantaged area.

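### The planned within-trial cost per new cancer diagnosed has no written denominator, and on any reading it would rest on very few cancers

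*Protocol article*

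**What the plan says.** The Health economic assessment section of the protocol article compares the intervention with usual care and names two results. The first is written out: the difference in cost between the arms, relative to the observed increase in testing, giving a cost per additional screening. The second is only named: "we will calculate the cost per new cancer diagnosed in patients with a positive screening test". Its numerator and denominator are not given. The section then fixes the horizon: "The time horizon of the analysis will be the duration of the study (1 year"). It describes no model that would carry results beyond the trial data.

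The abstract gives the size as "32 GPs primarily serving underserved populations across four regions in France with 1024 patients recruited". The Sample size and power calculation section sizes the trial on uptake, "to detect a 15% difference between the control and intervention arm in CRC screening uptake". Nowhere does the article give an expected number of cancers, a FIT positivity rate or a predictive value.

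**The concern.** A cancer is counted only if a patient takes the test, the test is positive, a colonoscopy follows and it finds cancer, all within the year. Each step removes most of those who remain. A trial sized for a difference in the first step can be ample for uptake and still have almost nothing to count at the last.

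A ratio with a denominator at or near zero has no stable value. One chance diagnosis in either arm can turn it from undefined to finite, or from negative to positive. Readers would still see it beside the cost per additional screening, which the trial can support.

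**Working it through.** **Inputs from the article**
- Patients: 32 GPs × 32 patients = 1024, which matches the abstract. With balanced allocation ("We will use block randomization to ensure a balanced allocation of each cluster (GP or GP office) in each region"), taken as 1:1, this is 512 per arm.
- Target difference in uptake: 15%, taken as percentage points (Sample size and power calculation).
- Control uptake: not given for the trial. The national 30.5% from the Background is used, so the intervention arm is 30.5% + 15% = 45.5%.

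**Assumptions, because the article gives no figure**
- FIT positivity 2% to 10% and predictive value for cancer 3% to 10%, with 4% and 8% as a middle case.
- Every positive test leads to colonoscopy, and every diagnosis falls inside the year. Both raise the count.
- Cancers in the two arms are independent Poisson counts.

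The plan has no cancer figure of its own to reproduce.

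**Step 1, people screened.** Intervention: 512 × 0.455 = 233. Control: 512 × 0.305 = 156. Difference: 512 × 0.15 = 76.8, about 77.

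**Step 2, expected cancers** = 512 × uptake × positivity × predictive value.

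| Positivity, predictive value | Per 1000 screened | Intervention | Control | Difference | Both arms |
|---|---|---|---|---|---|
| 2%, 3% | 0.6 | 0.14 | 0.09 | 0.05 | 0.23 |
| 4%, 8% | 3.2 | 0.75 | 0.50 | 0.25 | 1.25 |
| 10%, 10% | 10 | 2.33 | 1.56 | 0.77 | 3.89 |

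One expected extra cancer would need 1 / 76.8 = 13 cancers per 1000 screened, above the whole assumed range.

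**Step 3, chance of an unusable denominator**, with the full 15-point gain in uptake achieved. The difference of two Poisson counts follows a Skellam distribution. The chance of no cancers is exp(−expected count).

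| Positivity, predictive value | Difference ≤ 0 | Difference ≤ 1 | None in intervention arm | None in either arm |
|---|---|---|---|---|
| 2%, 3% | 88% | 99% | 87% | 79% |
| 4%, 8% | 63% | 88% | 47% | 29% |
| 10%, 10% | 45% | 66% | 10% | 2% |

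**Step 4, sensitivity**
- Uptake 60% versus 45%: the expected difference is unchanged at 0.05 to 0.77, because it depends only on the 15 points. The chance that it is zero or below is 85% to 46%.
- The stated 25% attrition applied to cancers (512 × 0.75 = 384 per arm): difference 0.03 to 0.58, chance of zero or below 91% to 49%. Data from the regional centres may avoid this loss, so 512 is the main case.
- Extreme uptake of 65% (top of the programme target) versus 30.5%, at 4% and 8%: 512 × 0.345 × 0.0032 = 0.57 extra cancers, chance of zero or below 51%.
- A narrower range, with positivity 3% to 8%, colonoscopy completion 80% to 100% and cancer in 4% to 10% of colonoscopies: difference 0.07 to 0.61, chance of zero or below 82% to 48%.

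**The case against.** The strongest objection concerns what the article commits to. A reader might infer that the second ratio divides by a between-arm difference, but the text writes out the incremental form only for the first. An average cost per detected cancer is an equally literal reading. On that reading a negative ratio cannot arise, and the 45% to 88% does not apply. This stands. The incremental reading is an inference from the comparison with usual care and from the form of the first ratio. It does not rescue the result, though, since the average over the intervention arm rests on 0.14 to 2.3 expected cancers and the pooled count on 0.2 to 3.9.

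A reader might also infer that an undefined or negative ratio is the most likely outcome throughout. It is not: at the top of the assumed range that chance is 45%. The range itself comes from outside the documents, and 88% combines the lowest positivity with the lowest predictive value. This also stands.

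Next, a one-paragraph economic section in an article may leave the exact ratio, its intervals and the handling of sparse counts to a fuller plan. That is fair for those details, and their absence is no fault. But the commitment to this ratio over this horizon is stated here, and defining it more fully would not add cancers.

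Finally, the economic assessment is not among the three aims, the abstract's methods or the outcome tables. It would be wrong to treat this as a flaw in a headline result or in the trial's main analysis.

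**Conclusion.** The point holds as a limited one. The article commits to a within-trial cost per new cancer diagnosed that about 1024 patients followed for one year cannot support, and it leaves the denominator undefined. Across the assumed inputs, the expected denominator is 0.05 to 0.8 cancers if incremental, 0.14 to 2.3 if averaged over the intervention arm and 0.2 to 3.9 if pooled. In the middle case the chance of an incremental denominator at zero or below is 63%, and the chance of no cancer in the intervention arm is 47%.

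The sizes rest on assumed positivity and predictive value, on the national uptake rate and on the full 15-point gain. A negative ratio further requires the incremental reading and an intervention that costs more than usual care. The assumptions of complete colonoscopy and in-year diagnosis are generous. The section also frames the analysis among patients with lower health literacy; if that is a restriction, the counts fall further.

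This is a secondary economic result. The primary outcome and the cost per additional screening do not depend on it.

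**What to change.** 1. Keep cost per additional screening as the within-trial ratio.
2. Report new cancers diagnosed after a positive test as a count in each arm, with exact intervals, beside the incremental cost and without a ratio.
3. If a cost per cancer is wanted, label it a scenario: the trial's uptake difference multiplied by external positivity and predictive value over a stated range, with its source and the colonoscopy completion assumed. At a 15-point difference, the range used here gives 0.15 × 0.0006 = 0.09 to 0.15 × 0.01 = 1.5 extra cancers per 1000 patients enrolled. The width of that range should be shown with the result.

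This costs a change of wording and an optional simple scenario calculation, with no new data collection or redesign. The downside is that one within-trial figure is lost or becomes model-based.

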### Data management and statistical analysis

### Data management

All data will be anonymized using ID codes for both GPs and participants. All data will be managed securely via MS Access databases, linked across the four sites via the secure data sharing system SCOUT, hosted by the University of Toulouse III Paul Sabatier. Access to data will be granted only to members of the study team. Data from questionnaires and interview transcripts will be kept for a period of 2 years after publication of the results is completed.

All data will be verified on entry into the systems and cleaned. An audit process of typically 10% of the data will also be completed on the T1 data prior to the T2 data being collected.

